**Objective:**

The aims of this study are to perform an adequately sized, nurse-led, long-term secondary preventive follow-up with inclusion of an unselected population of ACS patients. The focus will be on lipid and blood pressure control as well as tobacco use and physical activity.

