### Hypothesis

We hypothesize that in ACS patients, this nurse-based, telephone follow-up will reduce risk factor levels more effectively than usual care.

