### Outcomes

Outcomes will be measured after 12, 24, and 36 months of follow-up. Outcome variables are total cholesterol, LDL cholesterol, and sitting systolic and diastolic blood pressure as well as the proportion of patients achieving the set target for these variables. Standing systolic and diastolic blood pressure, smoking rates, the proportion of patients treated with different secondary preventive drugs, diabetes control by Hb1C, and change in body mass index (BMI) and physical activity will also be measured. The LDL value at 36 months will be analyzed as the primary outcome. Analyses of the secondary outcomes will be exploratory. Blood pressure measurements are standardized as described above, and LDL values are calculated from the serum concentrations of cholesterol and fasting triglycerides using the Friedewald formula. Smoking (yes/no) and physical activity (duration/week) are self reported. Deaths are available in the hospital records and will be recorded to detect any survival difference between groups.

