### Sample Size

A difference between groups in mean LDL of 0.5 mmol/L and in mean systolic blood pressure of 5 mmHg is considered clinically relevant and requires study groups of approximately 200 participants to be reliably detected (alpha .05, two-tailed, power 80%). Study groups of at least 250 participants are planned to allow for drop-outs. This sample size is also adequate for detection of clinically meaningful group differences in smoking rates (10%), proportion reaching treatment goals (10%), change in BMI (1.0), and change in physical activity (10%, proportion in a given activity level), calculated with two-tailed alpha .05, power 80%.

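### Systolic blood pressure helps set the sample size but is left exploratory: the outcome hierarchy does not match the sample-size basis, and a fixed sequence after LDL would repair this without extra patients

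*Protocol article*

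**What the plan says.** The relevant statements are all in the protocol article.

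- **Abstract, Objective:** "The focus will be on lipid and blood pressure control as well as tobacco use and physical activity". Four areas are named, with lipids and blood pressure first.
- **Hypothesis:** the expectation is that "this nurse-based, telephone follow-up will reduce risk factor levels more effectively than usual care". No single variable is named.
- **Sample Size:** "A difference between groups in mean LDL of 0.5 mmol/L and in mean systolic blood pressure of 5 mmHg is considered clinically relevant". About 200 per group are said to be needed for these two differences at two-tailed alpha .05 and 80% power. Then: "Study groups of at least 250 participants are planned to allow for drop-outs". The Abstract's Methods paragraph likewise ties the 250 per group to the LDL and systolic differences. Smoking rates, goal attainment, BMI and physical activity follow in a separate sentence, as further targets for which the size is also considered adequate.
- **Outcomes:** "The LDL value at 36 months will be analyzed as the primary outcome. Analyses of the secondary outcomes will be exploratory". Sitting systolic pressure is a listed outcome at 12, 24 and 36 months. Since it is not the primary outcome, it is exploratory.
- **Statistical Methods:** continuous secondary outcomes use the primary regression model. Every test is two-sided and is called significant below .05. No testing order is given.

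**The concern.** The Sample Size section puts systolic pressure level with LDL and ahead of the other risk factors. The Outcomes section removes that ranking without giving a reason, so systolic pressure has the same standing as BMI or drug use. The Statistical Methods section then applies the .05 threshold to all tests alike. A systolic P value below .05 would thus be exploratory under one section and significant under another.

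What is at stake is the strength of the conclusion on blood pressure. The trial recruits enough patients for a properly powered test of 5 mmHg but has no place for that test in its hierarchy. A claim that the method works as secondary prevention would have error-controlled support from LDL only, and a favourable systolic result could be offered only as supporting evidence.

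**Working it through.** **Inputs from the protocol article:** differences of 0.5 mmol/L (LDL) and 5 mmHg (systolic), two-sided alpha .05, power 80%, about 200 per group, at least 250 planned (Sample Size); allocation 1:1 (Trial Design). **Not given:** any SD. The SDs below are therefore either solved for or assumed over a range.

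**1. The plan's own figure.** With the normal approximation for two means,

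n per group = 2 × (1.960 + 0.842)² × SD² / difference² = 15.70 × SD² / difference².

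The figure of 200 cannot be reproduced directly without an SD, so the formula is solved for it: SD = difference / (2.802 × √(2/200)) = difference / 0.2802.

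- Systolic: 5 / 0.2802 = 17.85 mmHg.
- LDL: 0.5 / 0.2802 = 1.78 mmol/L.

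The step from 200 to 250 corresponds to a 20% drop-out rate (200 / 0.80 = 250), although no rate is stated.

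**2. Which outcome drives the size?**

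| Outcome | SD (assumed) | n per group |
|---|---|---|
| Systolic, 5 mmHg | 16 | 161 |
| Systolic, 5 mmHg | 18 | 204 |
| Systolic, 5 mmHg | 20 | 252 |
| LDL, 0.5 mmol/L | 0.8 | 41 |
| LDL, 0.5 mmol/L | 1.0 | 63 |
| LDL, 0.5 mmol/L | 1.2 | 91 |

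For example, LDL at SD 1.2: 15.70 × 1.44 / 0.25 = 90.4, rounded up to 91. At 200 per group, LDL power is 98.6% at SD 1.2 and higher at smaller SDs. If the LDL SD lies between 0.8 and 1.2, LDL is not what brings the size to 200; a systolic SD near 17.85 does.

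**3. What a fixed sequence would give.** Test LDL at 36 months at two-sided .05. Only if it is significant, test systolic pressure at 36 months at two-sided .05. The family-wise error over the two tests stays at or below .05. With 200 evaluable per group and a systolic SD of 17.85, the systolic test keeps 80% power. If the two tests are treated as independent, power to succeed on both is 0.9863 × 0.80 = 0.789 at LDL SD 1.2, and 0.80 at SD 0.8.

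**4. The alternatives.**

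- Two primary outcomes, each at .05 without adjustment: family-wise error 1 − 0.95² = 0.0975 if independent.
- Two primary outcomes at .025 each: n = 2 × (2.241 + 0.842)² × 17.85² / 25, about 243 evaluable per group, or 243 / 0.80 = about 304 recruited. Staying at 200 evaluable leaves about 71% systolic power.

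The fixed sequence is the only one of the three that controls the error without extra patients or lost power.

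**The case against.** The strongest reply is that nothing here is wrong. One primary outcome with openly exploratory secondaries is a legitimate way to protect the type I error, and powering a trial for a secondary outcome does not oblige anyone to make it confirmatory. The Sample Size section also claims adequate power for smoking, goal attainment, BMI and activity, and nobody would promote all of those. Testing order among secondaries is often left to an analysis plan, and none is shown here. Most of this stands, and it is why the point concerns a mismatch rather than a mistake. It does not dispose of the point. The Outcomes section itself fixes the hierarchy, and the Sample Size section sets systolic pressure apart from the other four targets by naming it together with LDL.

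Three stronger readings are tempting but are not supported:

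- *Half of the main objective is lost.* The objective names four areas, and the hypothesis speaks of risk factors in general.
- *Nothing can ever be concluded on blood pressure.* Systolic pressure is pre-specified, measured at three time points and analysed with the primary model. It will yield an adjusted randomised estimate and a P value, which is weaker evidence but still evidence.
- *Two-thirds or more of the patients serve only systolic pressure.* The surplus over LDL's need depends on assumed SDs. At an LDL SD of 1.2 it is (200 − 91) / 200, about 55%. Other targets may use it too: an assumed smoking rate of 20% against 10% needs about 199 per group. Every patient also adds precision for LDL.

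The error-rate problem is conditional as well. It arises only if an exploratory systolic result is later presented as confirmatory.

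**Conclusion.** The point holds as a mismatch between the outcome hierarchy and the sample-size basis. Systolic pressure is a sizing target named together with LDL and a stated focus of the trial, yet any systolic finding can only be supportive. The primary LDL analysis and its error control are unaffected, so this is a worthwhile improvement that has been missed rather than a flaw in the main result.

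Its size rests on SDs that the article does not give: about 17.85 mmHg for systolic pressure, solved from the stated 200 per group, and 0.8 to 1.2 mmol/L assumed for LDL. If the true systolic SD were 20 mmHg, power for 5 mmHg at 200 per group would be about 70% instead of 80%. A confirmatory systolic test would then be less well supported, but would still cost nothing to include.

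**What to change.** Amend the Outcomes and Statistical Methods sections to name sitting systolic blood pressure at 36 months as the single key secondary outcome. Test it with the primary regression model at two-sided .05 only if LDL at 36 months is significant. State that all other outcomes and time points remain exploratory.

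Because the study is recruiting and registered, this needs a dated amendment made before any between-group data are seen.

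The cost is that amendment. It requires no additional patients or measurements, takes no alpha from LDL and leaves the primary analysis unchanged. The one drawback is that systolic pressure stays exploratory if LDL is not significant. With a true LDL difference of 0.5 mmol/L and an SD up to 1.2, the chance of that at 200 per group is about 1.4% (1 − 0.9863); it rises if the true difference is smaller.

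If the sponsor prefers to keep the present hierarchy, the minimum is a sentence saying that conclusions on blood pressure will be exploratory whatever the P value.

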### Sample Size

A difference between groups in mean LDL of 0.5 mmol/L and in mean systolic blood pressure of 5 mmHg is considered clinically relevant and requires study groups of approximately 200 participants to be reliably detected (alpha .05, two-tailed, power 80%). Study groups of at least 250 participants are planned to allow for drop-outs. This sample size is also adequate for detection of clinically meaningful group differences in smoking rates (10%), proportion reaching treatment goals (10%), change in BMI (1.0), and change in physical activity (10%, proportion in a given activity level), calculated with two-tailed alpha .05, power 80%.

### Randomization

The random allocation sequence will be computer generated in blocks of four and stratified for sex and type of ACS (unstable angina or myocardial infarction). A sealed, colored envelope will have a serial number on the outside and a folded sheet of paper inside with the group allocation written on it, which will be impossible to read from the outside. The study coordinators will enroll participants and assign them to interventions in order according to the serial number. The random allocation sequence will be computer generated by the study manager, who is not involved in the randomization process.

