## Methods

### Trial Design

This study is planned as a randomized, controlled trial with two parallel groups and an allocation ratio of 1:1.

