## Results

The study is ongoing and recruitment of participants will continue until December 31, 2014.

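### Fixed blocks of four, with the same coordinators enrolling and assigning at one hospital, weaken allocation concealment: up to one allocation in three could be deduced

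*Protocol article*

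**What the plan says.** The Trial Design section gives "two parallel groups and an allocation ratio of 1:1". The Randomization section fixes the method: "The random allocation sequence will be computer generated in blocks of four and stratified for sex and type of ACS". It describes the carrier: "A sealed, colored envelope will have a serial number on the outside and a folded sheet of paper inside", with the group written on that sheet, "which will be impossible to read from the outside". On roles it says "The study coordinators will enroll participants and assign them to interventions in order according to the serial number", and separately "The random allocation sequence will be computer generated by the study manager, who is not involved in the randomization process".

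Three other parts of the article bear on the point:

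- **Setting.** The Participants section names a single hospital for the whole county.
- **Visibility of the arms.** Under Interventions, a study nurse and a study physician manage one arm, while the patient's own physician manages the other. The article makes no statement about blinding, so openness is an inference, but a safe one.
- **Timing.** The Results section says "The study is ongoing and recruitment of participants will continue until December 31, 2014", so the block size became public during enrolment.

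**The concern.** Permuted blocks of a fixed, small size have a known weakness when the people who enrol can see earlier allocations: the end of each block gives itself away. Here several conditions for that come together. One team at one hospital sees every allocation, so blocks are not spread over sites. Sex and type of ACS are both known at enrolment. The arms cannot be confused once assigned.

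If the next allocation can be foreseen, it can influence who is approached or when. Some room for that exists. Whether a patient can manage telephone contact, and whether other disease is too severe, call for judgement. Inclusion happens at some point during the hospital stay, so the moment of consent can move a little.

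At stake is comparability of the arms for the primary outcome, LDL at 36 months. The primary model adjusts only for sex and type of ACS. If patients were enrolled selectively by frailty or expected adherence, the primary analysis would not correct for it. Other baseline covariates enter only in exploratory analyses.

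**Working it through.** The article gives no predictability figure to reproduce, so the check starts from the design.

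**Inputs**

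- Block size 4, with no variation mentioned (Randomization)
- Ratio 1:1, so each block holds two of each arm (Trial Design)
- Strata: 2 × 2 = 4 (Randomization)
- At least 250 per group, so about 500 in total (Sample Size)
- Assumption: an observer knows the block size, the block boundaries and all earlier allocations in the stratum

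**Fixed blocks of four.** There are 4!/(2!·2!) = 6 equally likely orders.

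| Position in block | Probability that the allocation is certain | Probability that the best guess is right |
|---|---|---|
| 1 | 0 | 1/2 |
| 2 | 0 | 2/3 |
| 3 | 1/3 (first two alike) | 1/3 × 1 + 2/3 × 1/2 = 2/3 |
| 4 | 1 | 1 |

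- Certain in advance: (0 + 0 + 1/3 + 1)/4 = 1/3 = 33.3%. Of 500 patients this is 500/3, about 167, or slightly fewer if the last block in a stratum is incomplete.
- Best guess right: (1/2 + 2/3 + 2/3 + 1)/4 = 17/24 = 70.8%.

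**Alternatives.** The fixed sizes are by exact enumeration. The mixed sizes are by simulation of 60,000 allocations, with an observer who knows the set of sizes but not the size of the current block.

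| Block sizes | Certain in advance | Best guess right |
|---|---|---|
| Fixed 4 (as planned) | 33.3% | 70.8% |
| Fixed 6 | 25.0% | 68.3% |
| Fixed 8 | 20.0% | 66.6% |
| Random 4, 6 | 5.4% | 69.3% |
| Random 2, 4, 6 | 4.3% | 70.4% |
| Random 4, 6, 8 | 2.0% | 68.1% |

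Two things follow. A larger fixed block helps little, because its end is still certain; what removes certainty is the variation in size. And no option brings the best-guess rate near 50%, so the gain lies in certainty and not in guessing.

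**Imbalance.** Within an unfinished block of size b, the arms can differ by at most b/2. That is 2 per stratum with blocks of four, and 4 when the largest block is eight. Over four strata the extremes are 4 × 2 = 8 and 4 × 4 = 16 patients, out of about 500.

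**The case against.** The strongest reply is that the article describes standard concealment measures: sealed envelopes that cannot be read, serial numbers, use in order, and a sequence produced by someone outside the randomization process. A reader might infer from the block arithmetic that allocation is not concealed at all. The document does not support that. These measures stop someone from reading the next allocation or obtaining the list, and partial predictability is not absence of concealment. They do not, however, address deduction from allocations already seen.

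Second, one in three is a ceiling. It requires staff to know the block size and boundaries and to keep a complete tally in each stratum. The article does not say that they do. Nor does it spell out that envelopes form a separate series per stratum, although envelopes prepared in advance and used in order can hardly deliver stratified blocks otherwise. Whether the block size was withheld from coordinators may be settled in a fuller protocol. This stands, and the point is conditional for that reason. But publication during recruitment made the block size available to anyone from then on.

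Third, the room for steering is limited. All hospitalized cases are to be assessed, all eligible patients are to be asked, and a test period found complete case identification. This also stands: it narrows the opportunity without closing it.

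Fourth, one might read the Discussion's statement about avoiding selection bias as contradicted by this design. It is not. That passage concerns which patients are recruited from the county, not how they are allocated.

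Finally, the figures measure predictability. They do not estimate any bias in LDL.

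**Conclusion.** The point holds as a weakness of concealment. Under the stated design, up to 33.3% of allocations are deducible with certainty and 70.8% can be guessed correctly. These figures are exact, given that staff know the block size and boundaries and track allocations by stratum. They also rest on the inference that allocation is visible once made. The document does not show that anyone used this knowledge, and the size of any effect on 36-month LDL cannot be derived from it. The claims that allocation is unconcealed, or that the trial result is biased, go further than the text allows. The case for acting is that the weakness can be largely removed at little cost while recruitment is still open.

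**What to change.** For the patients still to be recruited:

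- The study manager regenerates the unused envelopes within each sex by ACS-type stratum, using randomly varying block sizes, for example 4, 6 and 8.
- The new sizes are withheld from enrolling staff and not published until recruitment ends.
- Each envelope is opened only after eligibility and consent have been recorded.

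The study manager already generates the list and should stay outside the assignment of individual patients, so the separation of roles that the article describes is kept.

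Certain allocations among the remaining patients fall from 33.3% to about 2%. The best-guess rate falls only to about 68%, and this should be said openly. Patients already enrolled are unaffected, and the article does not say how many remain.

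The cost is one new list and a new set of envelopes. Imbalance within a stratum can be slightly larger: at most 4 from an unfinished block of eight, plus at most 2 if the switch cuts short a block of four, so 6 at the extreme against 2 now. The primary model already adjusts for both stratification factors, so the analysis need not change.

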### Statistical Methods

Mean values of blood pressure and lipid variables in the intervention and control groups will be compared using the *t* test for independent groups. Proportions will be compared using the chi-square test. The primary analysis will be performed according to the intention-to-treat principle using a linear regression model adjusting for sex and type of ACS. The adjustment is made to reflect the stratified randomization process. Per protocol analyses will also be performed. Secondary outcomes will be analyzed using the primary analysis model when continuous, and a logistic regression model, adjusting for the same covariates, when outcomes are binary. To assess indications of differential treatment effects across subgroups (ie, age, sex, comorbidity, level of education, and social classification), tests for interaction will be performed, although this aim is secondary because the study is not powered for this particular purpose. Adjustment for relevant baseline covariates will be performed in additional exploratory analyses of primary and secondary outcomes to evaluate the effect of possible baseline imbalance. All tests will be two-sided, and a *P* value of <.05 will be considered significant.

## Results

The study is ongoing and recruitment of participants will continue until December 31, 2014.

## Discussion

### Summary

Different approaches have been used to recruit patients for secondary prevention studies after an ACS. Some have involved contacting patients participating in rehabilitation programs [5], and others have identified patients with a previous diagnosis of coronary artery disease [6]. To avoid selection bias, a population-based approach is preferable and is the only way to obtain a reliable estimate of the proportion of excluded patients. Enrollment of the patients immediately after an acute event is probably the best way to achieve a high participation rate. This study covers all patients in a Swedish county, who will be eligible for inclusion after an ACS, thus avoiding selection bias. Thus, the study population will include even very old and very sick ACS patients, who are usually not part of randomized ACS studies. Their ability to participate in secondary prevention programs and their tolerability of medication when attempting to achieve set treatment goals are of great interest because these factors could have significant consequences for health economics and morbidity and mortality rates. The immediate recruitment and the logistics for including each and every ACS patient will show the true proportion of possible participants in the secondary preventive program.

A randomized design is necessary to reliably evaluate the effect of the intervention. Some investigators use a prospective cohort design, which makes it difficult to draw conclusions in terms of efficacy, particularly if the drop-out rate is high [12]. The design of the present study means that patients in the usual care group will be contacted by the study nurses to collect data about risk factors. This step adds a certain interference and possibly improvement in usual care but cannot be avoided if the results of the two groups are to be compared. The standard of care that is achieved in the intervention and control group can be assessed by comparing lipid and blood pressure values as well as other risk factor results with the corresponding values in other ACS populations.

We use an associated study physician for the intervention group to obtain immediate decisions about more qualified treatment changes. Based on the results of previous studies, rapid treatment decisions by someone directly involved in the study are related to more effective risk factor control [13].

The duration of follow-up has varied substantially among studies [8,14]. A follow-up period of at least 12-24 months seems necessary to evaluate the intervention during a clinically relevant period of time.

Different treatment goals for lipids and blood pressure have been used in different trials, but an LDL goal of <2.5 mmol/L and a blood pressure goal of <140/<90 are common [8]. These goals correspond well to recent American Heart Association /American College of Cardiology Foundation guidelines [15]. An option to treat lipids more aggressively in very high-risk patients with an LDL goal <1.8 mmol/L is included but given a lower class of recommendation. An LDL goal of <1.8 mmol/L in patients at very high cardiovascular disease risk is recommended in the recent European Society of Cardiology guidelines [16]. However, hard endpoint data from clinical trials using defined treatment goals are still lacking.

Secondary prevention after an ACS needs to be improved and to include a larger proportion of the patients. Importantly, the treatment goals need to be maintained over the long term. Even in trials that largely rely on telephone follow-up, the proportion of the target population eventually included has so far been small [5,6,17].

